Another well-established risk factor for PTB is the length of the uterine cervix. A cervical length of less than 25 mm between the 16th and 24th gestational weeks is a strong independent predictor of spontaneous PTB. The risk of PTB in these cases is estimated at 25–30% in women with no history of PTB and up to 35% in pregnant women who have previously presented PTB. If the length is under 15 mm, the risk of PTB reaches 50%. In fact, several authors indicate the need for screening cervical length in this period via transvaginal ultrasound [8,9]. The management of cervical shortening (CS) includes the topical administration of progesterone, the use of pessary, and cerclage. A recent meta-analysis detected a significant reduction in the rate of extreme prematurity (< 33 weeks of gestation, < 2,500 grams birth weight) in pregnant women with CS (< 25 mm) who used intravaginal progesterone daily [9].

A common factor for the aforementioned conditions is the possibility of implementing preventive measures. Identifying risk factors for PTB early and before the development of irreversible clinical symptoms (e.g. cervical dilation, intraamniotic infection, oxidative damage associated inflammation) enables a personalized approach to patient care, aiming to reduce the risk of preterm birth and its sequelae. Thus, the primary aim of this study protocol is to reduce PTB in pregnant women from Health Units in the city of Jaú - SP, Brazil by implementing a low-cost bundle to assess and manage major modifiable risk factors for PTB. The secondary aim is to demonstrate the feasibility of our implementation protocol.

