**Figure 1. f0001:**
[figure not shown]
Temporal flowchart of cluster inclusion (health units) in the quasi-experimental design study.

During the first 18 months, all first-trimester pregnant women from eight randomized UBS/USF (clusters) are being included. In the next step of the study, 2 UBS/USF per month will be included until all primary care units (clusters) in the municipality are included, as demonstrated in Figure 1.

All pregnant women of eligible gestational age from the eight initially randomized health units were systematically invited to participate in the study and referred to Gestar. Cluster randomization was performed using a randomization tool (https://www.random.org/). Allocation was concealed and known exclusively by the coordinating researcher until implementation, minimizing the risk of selection bias. All participants included in the study will be monitored until the gestational outcome through three appointments, one in each gestational trimester. The inclusion criteria for the study are singleton pregnancy and gestational age between 11 weeks and 13 weeks and 6 days at the first appointment, defined by ultrasound. Pregnancies with fetal death and those attending fewer than two study appointments (first and second trimester) will be excluded from the study.

Considering the intervention aims to reduce the preterm birth rate from 18% (baseline rate, DataSUS) to 11.5% (São Paulo state rate = target rate), with 95% confidence, 5% margin of error, and 80% statistical power, the minimum sample size calculated is 201 patients (SAS 3.0 software). Adjusting the sample size to account for cluster effects (DE = 1+(m − 1)×ICC, where DE: design effect; mean cluster size: *m* = 20; intra-cluster correlation coefficient: ICC = 0.01), the conventional individual-based sample of 201 increased to 240. Considering a 20% loss to follow-up, the final sample size will be 300 participants.

To reduce cross-contamination, clinical procedures are centralized at a reference site (Gestar), and the distribution of printed and digital protocols to the Health Units are restricted until activation. A 2-week operational wash-in with adherence monitoring was implemented.

This project was approved by the Research Ethics Committee of Unoeste – Universidade do Oeste Paulista (CAAE 63,623,922.70000.5515). All patients involved will be informed about the research and sign the informed consent form.

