Below is a detailed description of each component of the intervention:(1) First Trimester (11 to 13 weeks and 6 days): Assessment and Smoking Intervention.**Sociodemographic and Clinical Assessment**: During the first trimester, participants undergo an initial interview to collect personal, social, and clinical information. This includes family and obstetric history, as well as smoking status.**Smoking Cessation Support**: Pregnant women identified as smokers who are willing to quit are provided with a comprehensive smoking cessation program. This includes referral to the city’s smoking prevention program, which is conducted at the Alcohol and Drug Psychosocial Care Center (CAPS-AD).The smoking intervention involves an initial interview and adjuvant treatment with auricular acupuncture. This technique uses pressure points in the ear to help reduce anxiety and withdrawal symptoms associated with smoking cessation.Acupuncture sessions are conducted every 15 days, where seeds are placed on specific points in the ear to stimulate them. Cotton and 70% alcohol are used to clean the ear, an auricular pressure gauge is used to locate the points, and mustard seeds with micropore are placed for acupressure of the selected points. The patients are instructed to stimulate these points themselves three times daily. Auriculotherapy is delivered by a trained and certified professional. Patient engagement is monitored by tracking attendance, with the number of appointments systematically recorded in the medical records.If necessary, group sessions with psychological support are provided at CAPS-AD, and pharmacological treatment, such as nicotine patches, may be used for gradual dose reduction to alleviate withdrawal symptoms.2. **Second Trimester (20 to 23 weeks and 6 days): Cervical Length Monitoring and Infection Treatment**.**Cervical Length Screening**: Between 20 and 24 weeks of gestation, all participating women undergo a transvaginal ultrasound to measure cervical length, a critical indicator of the risk for PTB.The measurement is taken with the patient in the lithotomy position, using a transvaginal probe to assess the distance between the internal and external orifices of the cervical canal. Women are instructed to empty their bladder before the ultrasound evaluation.Three consecutive measures are taken and the smallest value is considered. If a cervical length of less than 25 mm is detected, the woman is diagnosed with cervical shortening.Women diagnosed with cervical shortening are prescribed 200 mg of vaginal progesterone daily until 36 weeks of gestation, aiming to reduce the risk of PTB. For these women, the measurement is repeated biweekly for follow-up and monitoring treatment adherence.For cases of severe cervical shortening, such as lengths below 15 mm, cerclage – a surgical procedure to reinforce the cervix – is considered, depending on the patient’s clinical history and ongoing evaluations.**Investigation and Treatment of Infections**: During the same trimester, women are also screened for lower genital tract infections using molecular tests for *Chlamydia trachomatis* and *Neisseria gonorrhoeae*. These investigations are performed at this time due to the less friable nature of mid-trimester cervices in comparison to the first trimester of pregnancy.The assessment includes a complete gynecological examination with swabs for Gram staining, vaginal pH measurement, and cytobrush sampling collection for PCR analysis of cervical infection using the automated Cobas® 4800 CT/NG v2.0.Identified infections are treated according to the local clinical protocols to ensure the health of both the mother and the fetus.

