
**3. Throughout All Trimesters (11 weeks to Term): Vaginal Microbiota Monitoring and Dysbiosis Management.**

**Quarterly Assessment of Vaginal Microbiota**: During each trimester, vaginal samples are collected from the vaginal wall using sterile swabs to assess eubiosis (the balance of the vaginal microbiota) by bacterioscopy using the Gram staining method according to the criteria set by Nugent et al. [11].The microscopic evaluation aims to identify dysbiosis, such as bacterial vaginosis, candidiasis, or other alterations in the vaginal microbiota. The trained examiner will be blinded to patients’ clinical symptoms and a quality assessment of the readings will be performed by an independent examiner, following the same criteria.Women diagnosed with dysbiosis receive treatment based on the type of condition identified. For bacterial vaginosis, standard antibiotic metronidazole 500 mg orally 12/12 h for 7 days regimens are administered. Recurrent cases are treated with metronidazole gel 0.75% 5 g intravaginally once a day for 5 days or Clindamycin cream 2% (20 mg/g) 5 g intravaginally at bedtime for 7 days, according to the CDC protocol, and the partner is treated with secnidazole orally 1000 mg, single dose.Standard antifungal treatment provided for candidiasis is topic nistatin for seven nights. Recurrent cases are treated with miconazole 2% cream 5 g intravaginally daily for 14 days.Additionally, all participants are educated on proper intimate hygiene practices to help maintain a balanced vaginal environment throughout the pregnancy.

This protocol is conducted alongside standard prenatal care and patients are periodically reminded of their appointments. The study protocol is original and was registered in the Brazilian Clinical Trial Registry (ReBec) on 29 October 2024 (approval pending).

Data regarding the appointments, patients’ compliance with the protocol, and pregnancy outcome will be collected through interviews and medical records by the researchers for subsequent analysis. Data entry will be double checked, periodically updated and securely stored in the institutional repository. Only the researchers will have access to individual-level data, while metadata will be made openly available after publication of the study results.

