### Analysis plan

The main outcome of interest is gestational age at birth, based on first-trimester ultrasound, to be compared between the participants of the study and the general population. For the analysis, gestational age will be treated as categorical data (preterm birth vs. term birth). The primary analysis will follow the intention-to-treat principle: participants will be analyzed according to the assignment of their cluster at the time of inclusion. Secondary analyses will consider gestational age at delivery (continuous, in days) and other perinatal outcomes.

Secondary outcomes include the percentage of pregnant women included, the percentage of complete follow-up, percentage of adherence to prescribed treatments, and neonatal outcome (Apgar score, birth weight, and length of stay in the Intensive Care Unit). Descriptive statistics will be performed to analyze clinical, biological, and sociodemographic data of the studied population. Vaginal microbiota status across the trimesters will be compared using the Chi-square test.

Logistic regression will be performed to evaluate the role of the protocol in reducing PTB. To minimize multiplicity in the analysis and interpretation, covariates for adjustment such as parity, maternal age, and socioeconomic status will be included. The primary effect estimate will be obtained from mixed-effects logistic regression models including a random intercept for cluster and fixed effects for period and pre-specified baseline covariates (maternal age, parity, socioeconomic status). Additional per-protocol analyses will be performed as sensitivity analyses and will include participants who received the defined intervention components. Missing data in covariates will be handled using multiple imputations (MICE) under a missing-at-random assumption. The level of significance adopted for the tests used will be 5%, using *Prism* 5.0 (GraphPad Software).

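### The attendance-based exclusion, applied as written, removes early drop-outs from the completion and first-visit adherence percentages and so inflates these feasibility measures

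*Protocol article*

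**What the plan says.** The Background section closes with the aims: "The secondary aim is to demonstrate the feasibility of our implementation protocol". The Analysis plan lists three process measures among the secondary outcomes that bear on that aim: "the percentage of pregnant women included, the percentage of complete follow-up, percentage of adherence to prescribed treatments". It gives no numerator or denominator for them.

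The Study design section (text after Figure 1) sets the follow-up schedule: "All participants included in the study will be monitored until the gestational outcome through three appointments, one in each gestational trimester". The same paragraph adds: "Pregnancies with fetal death and those attending fewer than two study appointments (first and second trimester) will be excluded from the study". The exclusion is from the study as a whole. It is not limited to the preterm-birth analysis.

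Under Interventions, the second appointment falls in the "Second Trimester (20 to 23 weeks and 6 days" window and carries the cervical-length scan and the cervical infection tests. Smoking support starts in the first trimester, and vaginal dysbiosis is assessed and treated in every trimester. Data on appointments and compliance are to be recorded, and "pregnancy outcome will be collected through interviews and medical records by the researchers for subsequent analysis".

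**The concern.** An exclusion based on attendance is combined with an outcome based on attendance. A woman who enrols in the first trimester and does not return for the second-trimester visit has missed central parts of the bundle, so for a feasibility aim she is a clear failure of implementation. If she is removed from the study, she leaves both the numerator and the denominator of the completion percentage, and the failure disappears. The same happens to adherence for any treatment she was prescribed at the first visit.

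The reported figures would then describe women already selected for having come back. A reader judging whether the programme keeps the women it enrols would see a rate that is too high, and could not tell by how much. This point concerns only the feasibility outcomes. How the exclusion affects the intention-to-treat analysis of preterm birth is a separate question.

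**Working it through.** **Inputs from the protocol (Study design, sample-size paragraph).** Individual sample 201; mean cluster size 20; ICC 0.01; loss to follow-up 20%; final sample 300.

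**Reproducing the plan's figures.**
- Design effect: 1 + (20 − 1) × 0.01 = 1.19.
- 201 × 1.19 = 239.19, rounded up to 240.
- 240 / (1 − 0.20) = 300. Both 240 and 300 reproduce.
- Planned loss: 300 × 0.20 = 60 women, leaving 240.

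**Effect of the exclusion on completion.** Let f be the share of the 60 losses that falls before the second appointment. The protocol does not give f, so the full range is shown.
- Over all enrolled: 240/300 = 80.0%, whatever f is.
- After the exclusion: 240 / (300 − 60f).

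| f (assumed) | Excluded | Over all enrolled | After the exclusion |
|---|---|---|---|
| 0 | 0 | 240/300 = 80.0% | 240/300 = 80.0% |
| 0.5 | 30 | 240/300 = 80.0% | 240/270 = 88.9% |
| 1 | 60 | 240/300 = 80.0% | 240/240 = 100% |

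**General form.** If s is the share of enrolled women lost before the second appointment, the overstatement factor is 1/(1 − s):
- s = 5%: 1/0.95 = 1.05
- s = 10%: 1/0.90 = 1.11
- s = 20%: 1/0.80 = 1.25

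**A milder assumed pattern.** Suppose 10% are lost before the second appointment and 5% of the remainder after it. Then 300 × 0.90 = 270 remain and 270 × 0.95 = 256.5 complete. Completion is 256.5/300 = 85.5% over all enrolled, but 256.5/270 = 95.0% after the exclusion.

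**Adherence.** The same factor applies to treatments prescribed at the first visit. Here s is the share of women prescribed that treatment who then miss the second visit, and those women are counted as non-adherent. Treatments that arise from the second visit are not affected, because women who miss that visit were never prescribed them.

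**The case against.** The strongest reply is that the Analysis plan names no denominator, so nothing says the percentage is taken after the exclusion. The sample-size paragraph counts loss against the 300 recruited, which suggests that all enrolled women could be intended. An article may also leave such definitions to a fuller document. This stands in part: a missing definition alone would be no finding, and the inflation depends on applying the exclusion as worded. But the exclusion is fixed in this text and reaches the whole study. A later document that counted these women would have to override it.

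It is also fair to say that 20% is a planning allowance and not a forecast, and that 100% requires every loss to come early. Both are true, which is why the result is given as a range.

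A reader might infer several stronger points that the document does not support:
- **Completion requires the third-trimester visit, so every early preterm birth counts as a follow-up failure.** The three-visit schedule makes this a possible reading. However, women are monitored up to the pregnancy outcome, and that outcome comes from interviews and records, so a woman who delivers early with a known outcome can be complete. No window is given for the third visit. If it were required and 2% to 4% delivered before it (assumed), the 95.0% above would fall to 95.0 × 0.98 = 93.1% or 95.0 × 0.96 = 91.2%. That is the opposite direction to the exclusion effect.
- **Periods with fewer early births would look more feasible.** No comparison of the feasibility outcomes between periods is planned.
- **All adherence figures lose these women.** Only treatments prescribed at the first visit are affected.

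**Conclusion.** The concern holds in a limited, conditional form. Applied as written, the exclusion removes early drop-outs from the completion percentage and from adherence to first-visit treatments, and inflates each by 1/(1 − share lost before the second appointment). On the plan's own 300 enrolled and 20% loss, completion would read between 80% and 100%, with 89% if half the loss is early. This rests on two assumptions: that the exclusion is applied to these denominators, which the wording implies and nothing in the article reverses, and the timing of the losses, which is unknown. If no loss precedes the second appointment, there is no inflation.

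It would go too far to say that the endpoint does not measure feasibility. The percentage included is reported separately, and completion still captures loss after the second visit. The matter is worth correcting because it touches a stated aim and is easily settled in advance.

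**What to change.** Add to the Analysis plan:
1. The attendance exclusion in the Study design section does not apply to the feasibility outcomes. Complete follow-up uses all women enrolled at the first appointment as its denominator.
2. Adherence to a prescribed treatment uses all women prescribed that treatment, including those who later miss the second appointment. All enrolled women would be the wrong denominator here, because it would count women who were prescribed nothing.

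As a clarification only, state that a woman who attended every appointment due before delivery and has a recorded birth outcome counts as complete.

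The cost is a few sentences and no new data, since appointments, compliance and pregnancy outcome are already to be collected. The downside is that the reported completion rate becomes less favourable.

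### An ordinary chi-square test is planned for vaginal microbiota readings taken repeatedly in the same women; its p-values are miscalibrated unless readings within a woman are uncorrelated (minor)

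*Protocol article*

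**What the plan says.** Three places in the protocol article bear on this.

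- **Study design** (Methods): "All participants included in the study will be monitored until the gestational outcome through three appointments, one in each gestational trimester". The same section says that "those attending fewer than two study appointments (first and second trimester) will be excluded from the study", so each analysed woman should contribute at least two readings.
- **Interventions, item 3**: "During each trimester, vaginal samples are collected from the vaginal wall using sterile swabs", read by Gram stain under the Nugent criteria. Between readings, "Women diagnosed with dysbiosis receive treatment based on the type of condition identified".
- **Analysis plan**: "Vaginal microbiota status across the trimesters will be compared using the Chi-square test", at the general 5% significance level. No pairing, matching or woman-level term is mentioned.

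The only model in the article that handles dependence is the mixed-effects logistic regression for preterm birth. Its random intercept is for health unit, not for woman.

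**The concern.** A chi-square test on a trimester-by-status table treats the three columns as three separate groups of women. Here they are the same women seen up to three times. Two readings on one woman are unlikely to be unrelated, and the test's reference distribution does not allow for that.

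What is at stake is limited but real. Dysbiosis management is one of the three areas of the bundle, and this is the only analysis the article names for microbiota status over time. If readings within a woman are positively correlated, a true change between trimesters could go undetected and be taken as failure of that component. If they are negatively correlated, chance change is declared too often.

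**Working it through.** **No figure to reproduce.** The article gives no sample size, power or p-value for this comparison. The check therefore asks how far the ordinary test departs from its nominal 5% level.

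**Inputs from the protocol article**
- Three readings per woman, one per trimester (Study design; Interventions, item 3).
- Significance level 5% (Analysis plan).
- 240 women before the allowance for loss: "the conventional individual-based sample of 201 increased to 240" (Study design). This gives 240 × 3 = 720 readings if all are complete. It is used for illustration only; women need attend only the first two visits, so some third readings will be missing.

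**Assumptions not in the documents**
- Dysbiosis prevalence of 25% in every trimester (no change), or a fall of 30/25/20%.
- The same phi between any two of a woman's readings, varied over a range.
- Status as yes/no.

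**Analytic step.** With n women and prevalence p, the variance of the difference between two trimester proportions is 2p(1 − p)/n if readings are independent, and 2p(1 − p)(1 − phi)/n if they are matched. The ordinary test always uses the first. With no true change, its statistic therefore behaves approximately as (1 − phi) times a chi-square variable with 2 degrees of freedom. The 5% critical value is 5.991, and the upper tail beyond x is exp(−x/2), so

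true level = exp(−2.996 / (1 − phi)).

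| phi | 2.996/(1 − phi) | true level |
|---|---|---|
| −0.20 | 2.497 | 8.2% |
| −0.10 | 2.724 | 6.6% |
| 0 | 2.996 | 5.0% |
| 0.05 | 3.154 | 4.3% |
| 0.10 | 3.329 | 3.6% |
| 0.16 | 3.567 | 2.8% |
| 0.30 | 4.280 | 1.4% |
| 0.45 | 5.447 | 0.4% |

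**Simulation.** 240 women, three complete readings, correlated binary data from a latent normal model, 10,000 runs per row:

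| phi | level: chi-square | level: Cochran's Q | power (30/25/20%): chi-square | power: Cochran's Q |
|---|---|---|---|---|
| 0 | 5.3% | 5.2% | 61% | 61% |
| 0.2 | 2.2% | 4.8% | 61% | 72% |
| 0.3 | 1.4% | 4.9% | 60% | 77% |
| 0.5 | 0.3% | 4.8% | 59% | 90% |

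The simulated levels agree with the formula. A second set (20% dysbiosis under no change, a fall of 20/16/12%, 4,000 runs) shows the same pattern. At phi of about 0.16, 0.30 and 0.45, the chi-square level is 2.7%, 1.7% and 0.5%. Power is 56%, 54% and 53%, against 63%, 70% and 82% for Cochran's Q.

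The matched test keeps its level throughout and gains power as phi rises. The ordinary test is correct only at phi = 0.

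**The case against.** **The wording may be loose.** McNemar's test and Cochran's Q are also referred to a chi-square distribution, and an analysis plan that is not shown might name one of them. But the article states a test rather than leaving it open, nothing in the sentence signals matching, and the same section does specify dependence where it is wanted, for preterm birth. As written, the statement is wrong.

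**The analysis is peripheral.** This stands. Microbiota status is neither the main outcome nor a listed secondary outcome, and the sentence follows directly on the descriptive statistics. Swabs are described only as part of the intervention, so the comparison is an uncontrolled before-after description. No p-value from it, matched or not, could show that the bundle controls dysbiosis.

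**A reader might infer that power is certainly lost.** The documents do not support that. It requires positive correlation, and they give no value. Treatment of affected women between readings may pull phi towards zero, where the error is small (4.3% at phi = 0.05), or even below it, where the direction reverses. Where phi is positive the test is conservative and does not produce excess false claims of change.

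**A reader might add that health-unit clustering is ignored.** A woman's readings come from the same unit, so a shared unit effect is common to all trimesters and largely cancels in a comparison between them. This is not part of the point.

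**A reader might also infer that drop-out of early deliverers imitates improvement.** The article does not say whether all available or only complete readings enter the test, and it gives no size for the link between dysbiosis and a missing third reading. As an illustration, assume 20% dysbiosis without true change, doubled preterm risk with dysbiosis, and every preterm deliverer missing visit 3. At an 11.5% preterm rate the risks are 9.58% and 19.17%, and third-trimester prevalence becomes 0.20 × 0.8083 / 0.885 = 18.3%. At 18% the risks are 15% and 30%, and it becomes 0.20 × 0.70 / 0.82 = 17.1%. The shift is modest even in this severe case. Nor does a matched test cure it: a complete-case Cochran's Q selects more strongly, and an unweighted GEE has the same changing denominator.

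**Conclusion.** The point holds as a minor one. The design gives repeated readings on the same women, and the named test assumes independence, so its p-values are miscalibrated for any non-zero within-woman correlation.

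The size depends wholly on phi, which the documents do not give. For assumed phi from 0.1 to 0.45, a nominal 5% test runs at about 3.6% to 0.4%. Its power shortfall against Cochran's Q is 17 percentage points at phi = 0.3 in one assumed scenario (77 − 60) and 16 in the other (70 − 54). At phi = -0.1 the level is about 6.6%. The power figures also rest on assumed prevalences, assumed falls and complete readings for 240 women.

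The primary preterm-birth analysis and the sample size are unaffected.

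**What to change.** Replace the chi-square sentence with a repeated-measures analysis:

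- **Outcome.** Define a yes/no status first: any dysbiosis, or bacterial vaginosis. Interventions, item 3, describes several types of alteration, and the methods below need a dichotomy.
- **Main analysis.** Mixed logistic regression with trimester as a factor and a woman-level random intercept, using all available readings. This keeps women without a third reading, under a missing-at-random assumption. A random intercept cannot represent negative correlation; if that is thought possible, a logistic GEE with woman as the clustering unit and robust standard errors is the alternative.
- **Check.** Cochran's Q for women with all three readings, or McNemar's test for a pair of trimesters.
- **Reporting.** Call the comparison descriptive and uncontrolled, and give the number of readings in each trimester.

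The cost is a sentence or two in the Analysis plan. No new data are needed, and the class of model is already planned for preterm birth. The article describes the study as ongoing, so the change can be made before analysis.
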